## Abstract

**Background:**

Chronic heart failure (CHF), the final stage of various cardiovascular diseases, is a major public health problem resulting in significant hospitalization rates, mortality, and huge health care costs despite advances in the treatment and management of heart failure and heart failure-related risk factors. *Qishen* granules (QSG), a Chinese herbal formula, is widely used by traditional Chinese medicine (TCM) practitioners to treat CHF. Several animal experimental studies have showed that QSG can significantly relieve the heart failure symptoms in CHF rat models. However, there is as yet no standard clinical trial to confirm this. Thus, the investigators are conducting this study to evaluate the efficacy and safety of QSG in a large, and varied population.

**Methods/design:**

This study is designed as a randomized, placebo-controlled, multi-center, double-blind clinical trial with parallel groups. A total of 200 patients with CHF will be recruited and randomly allocated to either the QSG treatment group or the placebo group (in a 1:1 ratio). The patients will receive QSG or placebo granules twice a day for 12 weeks. The primary outcome is the proportion of patients in the QSG group, compared with the placebo group, demonstrating a more than 30% decrease in NT-proBNP level during 12 weeks of treatment. The secondary outcomes consist of composite cardiac events, New York Heart Association functional classification, 6-minute walking distance, left ventricular ejection fraction, patient quality of life, and the TCM syndrome integral scale.

**Discussion:**

On a background of standard treatment, QSG may further reduce the levels of NT-proBNP. This trial will provide high-quality evidence on the efficacy and safety of QSG in treating CHF, thus providing reference for clinical application of QSG.

**Trial registration:**

Clinical Trials.gov: NCT03027375. Registered on 16 January 2017.

**Electronic supplementary material:**

The online version of this article (doi:10.1186/s13063-017-2193-z) contains supplementary material, which is available to authorized users.

## Background

Chronic heart failure (CHF), the final stage of various myocardial diseases, is a chronic clinical syndrome that occurs when the heart is unable to pump blood within the circulatory system and organs cannot receive sufficient oxygen and nutrients [1]. Evidence from the American Heart Association’s report has demonstrated that the 2013 overall death rate attributable to cardiovascular disease was 222.9 per 100,000 Americans, of which 269.8 were men and 184.8 were women [2]. Meanwhile, despite advances in the treatment strategy for heart failure, such as evidence-based approaches to treat heart failure risk factors and implementation of angiotensin-converting enzyme inhibitors, β-blockers, coronary revascularization, implantable cardioverter-defibrillators, and cardiac resynchronization therapeutic strategies, the outcome often remains unsatisfactory. The most recent data from an international congestive heart failure prospective cohort study demonstrated that overall mortality within 1 year was 16.5% [3].

Traditional Chinese medicine (TCM), with a much lower cost and a significant curative effect on CHF-related symptoms, has been widely used in the treatment of CHF in China [4]. From the perspective of TCM, the primary cause of heart failure is heart *Qi* deficiency and blood stasis. *Qishen* granules (QSG) are prepared from a composition of six TCM herbs, including *Astragalus membranaceus* (Fisch.) Bge. var. *mongolicus* (Bge.) Hsiao, *Salvia miltiorrhiza* Bge., *Lonicera japonica* Thunb., *Scrophularia ningpoensis* Hemsl., *Aconitum carmichaeli* Debx., and *Glycyrrhiza uralensis* Fisch. This formula is widely used to treat the CHF of *Qi* deficiency and the blood stasis syndrome. Several animal experimental studies have showed the effect of QSG on the heart failure symptoms in CHF rat models [5–9], but there is yet no standard clinical evidence. Therefore, the investigators have designed a clinical study to assess the efficacy and safety of QSG in a large and varied population.

## Methods/design

### Objective

The objective of this study is to evaluate the safety and efficacy of QSG in a large and varied CHF population.

### Design

This study is designed as a randomized, placebo-controlled, double-blind, parallel-group, multi-center study in three tertiary academic medical centers of China to evaluate the safety and efficacy of QSG. The flowchart is represented in Fig. 1. The Standard Protocol Items: Recommendations for Interventional Trials (SPIRIT) Checklist can be found in Additional file 1.

**Fig. 1 Fig1:**
[figure not shown]
Flowchart of this study

Patient enrollment is expected to last up to 12 months. The end of the study is defined by the final follow-up of the last enrolled patient. This trial has been registered at ClinicalTrials.gov (ID: NCT03027375).

Qualified patients will be randomized into either of the two groups: the QSG treatment group or the placebo group (in a 1:1 ratio). Each group will receive either QSG or placebo granules in addition to standard care and appropriate medical support prescribed for CHF, which will be prescribed by the attending physicians based on the Chinese guidelines published in 2014 for the diagnosis and treatment of heart failure [10].

Recruited patients will receive QSG or placebo granules twice a day for 12 weeks. The QSG and placebo used in this study will be manufactured in China in accordance with the China Pharmacopoeia standard of quality control.

### Setting

There are three tertiary, academic medical centers participating in this study (China-Japan Friendship Hospital, Zhengzhou Hospital of Traditional Chinese Medicine, and Beijing Anzhen Hospital), all of which will provide original Case Report Form (CRF) tables to the central QSG office at Beijing University of Chinese Medicine.

## Recruitment

Through advertisements and referrals, a total of 200 patients who qualify will be recruited at the three centers participating in this study. A principle investigator, assisted by a well-trained study coordinator in each participating center, will identify potentially eligible patients based on the eligibility criteria. And, in collaboration with the attending physician, they will confirm the patient eligibility for the trial. The study coordinator will then obtain written informed consent from the patient, which will be obtained from participating clinicians before or at the time of patient consent.

### Eligibility, exclusion, and withdrawal criteria

The eligibility criteria are as follows: (1) age between 18 and 75 years, (2) clinical findings of CHF for at least 3 months prior to screening, (3) CHF caused by coronary heart disease and hypertension, which is diagnosed according to the Chinese guidelines published in 2014 [10] for the diagnosis and treatment of heart failure, (4) in a clinically stable condition with a New York Heart Association (NYHA) functional class of II to III and an optimal medical treatment with a fixed dosage for at least 2 weeks, (5) a documented left ventricular ejection fraction (LVEF) ≤ 40% and a serum *N*-terminal pro-B-type natriuretic peptide (NT-proBNP) level ≥ 450 pg/ml, (6) CHF of *Qi* deficiency and blood stasis syndrome based on TCM syndrome differentiation, and (7) provision of written informed consent.

The exclusion criteria are stated as below: (1) CHF accompanied by severe valvular heart disease, congenital heart disease, pericardial disease, cardiomyopathy, unstable angina, acute myocardial infarction (in the recent 4 weeks), cardiogenic shock, acute myocarditis, infective endocarditis, or uncontrolled severe cardiac arrhythmia with hemodynamic changes; (2) pulmonary heart disease, pulmonary hypertension caused by acute or chronic pulmonary embolism or cerebral apoplexy in the last 6 months; (3) severe hepatic inadequacy with alanine aminotransferase or alkaline phosphatase levels more than twice the upper normal limit, renal inadequacy with a serum creatinine level > 3 mg/dl (>265 μmol/L), severe electrolyte imbalance, severe hematologic disease, malignant tumor, diabetes mellitus with severe complications, or severe endocrine diseases such as hyperthyroidism and hypothyroidism; (4) acute infection confirmed by any one of the following three indicators: (a) fever, (b) a white blood cell count > 10 × 10^9^/L and a percentage of neutrophils > 75%, (c) shadow on chest X-ray, (d) uncontrolled blood pressure or fibrosis in other organs, (e) CHF of *yin* deficiency according to TCM syndrome differentiation, (f) pregnancy or breastfeeding, (g) psychiatric or infectious disease, and (h) patients who have participated in other clinical trials in the past 2 months.

The rejection and withdrawal criteria are listed as below: (1) unsuitability as judged by the investigators, (2) participants not following the protocol, (3) no visit record after treatment, and (4) voluntary withdrawal from the trial without any available data. These data will not be excluded from the study, instead, they will fall within ITT (intention-to-treat) through discussions among investigators, statisticians, data management, and others before un-blinding.

### Ethics

This trial has been authorized by the Institutional Review Board of Beijing University of Chinese Medicine (approval number: 2017 BZHYL0101). The research team will ensure this study be conducted in accordance with the principles of the Declaration of Helsinki [11] and the principles of Good Clinical Practice [12]. Signed informed Consent Forms will be obtained from all qualified participants before enrollment.

## Randomization

An independent statistician who is unaware of the design and purpose of the study will generate a randomization table by using Statistical Analysis System (SAS, version 9.4). The 200 patients will be randomly allocated in a 1:1 ratio to either the QSG treatment group or the placebo group. The randomization will be stratified by study site. According to the design of the random program, the researcher will open one random envelope and obtain a randomization number for a patient on the day of inclusion. Both investigators and participants will be blind to the allocations.

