### Primary outcome

The primary outcome is the proportion of patients in the QSG group, compared with the placebo group, demonstrating a more than 30% decrease in NT-proBNP level during 12 weeks of treatment.

On the day of inclusion, serum NT-proBNP will be taken as the baseline level of participants who will be enrolled and randomized for this trial before taking the QSG or placebo.

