## Statistical analysis

### Sample size calculation

The sample size was calculated based on the expected reduction in serum NT-proBNP levels during the study. Previous studies showed that the prognosis of patients with an NT-proBNP level decrease by at least 30% from baseline through treatment is better than in those not treated [14, 15]. Therefore, according to another previous study on treating CHF with Chinese herbal medicine [4], the proportion of patients demonstrating a more than 30% decrease in NT-proBNP level in the placebo group is 31.98% (*P*
_1_ = 0.3198). According to previous clinical results, the investigators assumed that the proportion of patients demonstrating a more than 30% decrease in NT-proBNP level in the QSG group would be 53% (*P*
_2_ = 0.53). Given a type-I error rate of *α* = 0.05 and a type-II error rate of *β* = 0.2, and considering a dropout rate of approximately 20% among randomized patients, the investigators plan to include a total of 200 subjects. The relevant formulas are shown as follows:$$ \mathrm{n}={\left({\mathrm{Z}}_{1-\alpha /2}+{\mathrm{Z}}_{1-\beta}\right)}^2\times \left[{\mathrm{P}}_1\left(1-{\mathrm{P}}_1\right)+{\mathrm{P}}_2\left(1-{\mathrm{P}}_2\right)\right]/{\delta}_2 $$
$$ \mathrm{N}=2{\mathrm{n}}^{\ast}\left(1+20\%\right) $$

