### Data analysis

Data entry and management will be completed by an independent data administrator to ensure data accuracy. A professional statistician will perform the data analysis for the results. We will use the intent-to-treat principle to analyze the efficacy and safety of QSG. For continuous variables, the independent two-sample Student’s *t* test will be used for comparisons between the two study groups, and the paired test will be used for intra-group comparisons. The *χ*2 test will be used for categorical variables. When continuous data distribution is not normal, the Wilcoxon test will be used. *P* < 0.05 is considered to be statistically significant, and all tests are two-tailed.

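### Randomization is stratified by site, but the only test named for the binary primary outcome is an unstratified chi-square test; an analysis by site and baseline NT-proBNP would be a free improvement

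*Protocol article*

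**What the plan says.** The Randomization section of the protocol article states that "The 200 patients will be randomly allocated in a 1:1 ratio to either the QSG treatment group or the placebo group" and that "The randomization will be stratified by study site". Under Setting it adds: "There are three tertiary, academic medical centers participating in this study". Site is the only stratification factor. Baseline NT-proBNP is not one, and no block size is given.

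The primary outcome is binary: each patient either is or is not a responder "demonstrating a more than 30% decrease in NT-proBNP level during 12 weeks of treatment". The same section provides for a sample before dosing in every enrolled patient: "serum NT-proBNP will be taken as the baseline level of participants".

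The Data analysis section assigns tests by type of variable. For the primary outcome the relevant rule is that the chi-square "test will be used for categorical variables". A P value below 0.05 "is considered to be statistically significant, and all tests are two-tailed". That section names no stratified test, site term or covariate. The Sample size calculation uses an unadjusted formula for two proportions.

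**The concern.** Suppose treatment is balanced within each site. Differences in response between sites then add nothing to the chance difference between arms. The plain chi-square test still counts them, because its variance comes from the pooled response rate. Its standard error is therefore too large for the design whenever sites differ, so the P value is slightly too large and some power is lost.

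Baseline NT-proBNP is a separate matter. It is measured in everyone before treatment and may predict a fall of more than 30%. Ignoring it leaves the test valid but gives up any precision it could add.

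What is at stake is a somewhat higher chance of missing a true effect, not a false claim of benefit. If the adjusted analysis is not fixed in advance, there is also later freedom to choose between adjusted and unadjusted results.

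**Working it through.** **1. The plan's own figure.** Inputs from the Sample size calculation: P1 = 0.3198 ("decrease in NT-proBNP level in the placebo group is 31.98" percent), P2 = 0.53, two-sided α = 0.05, β = 0.2, inflation by 1.2.

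n = (1.960 + 0.842)² × [0.3198 × 0.6802 + 0.53 × 0.47] / 0.2102² = 7.849 × 0.46663 / 0.044184 = 82.9, so 83 per arm.

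N = 2 × 82.9 × 1.2 = 198.9 (199.2 with n rounded to 83), against the stated 200. The figure reproduces. With 83 per arm, the unadjusted comparison has power of 80.0% (unpooled variance) or 78.7% (pooled variance, as in the chi-square test). The sizing already assumes an analysis without site or baseline.

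**2. True size of the plain test, analytically.** Take three equal sites with response rates p₁, p₂, p₃, mean p̄, and allocation balanced within site. The test uses the total variance p̄(1 − p̄), but the variance that applies is the mean of pₖ(1 − pₖ). With r = within-site / total, true size = 2[1 − Φ(1.96/√r)]. The site rates below are assumptions, because the protocol gives none.

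| Site rates | r | True size |
|---|---|---|
| 32/32/32% | 1.000 | 0.050 |
| 27/32/37% | 0.992 | 0.049 |
| 22/31/43% | 0.966 | 0.046 |
| 13/29/53% | 0.875 | 0.036 |

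For the third row, p̄ = 0.32, total = 0.2176, within = (0.1716 + 0.2139 + 0.2451)/3 = 0.2102 and r = 0.966.

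**3. Simulation, site effect only.** 166 patients, three near-equal sites, blocks of 4 within site, overall rates 31.98% and 53%. There were 10,000 runs per row, except 4,000 in the first.

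| Placebo site rates | Size, chi-square | Size, CMH | Power, chi-square | Power, CMH |
|---|---|---|---|---|
| 32/32/32% | 0.054 | 0.054 | 78.6% | 78.6% |
| 27/32/37% | 0.050 | 0.050 | 78.5% | 78.6% |
| 22/31/43% | 0.046 | 0.052 | 79.0% | 79.7% |
| 13/29/53% | 0.039 | 0.051 | 80.7% | 84.4% |

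The Monte Carlo standard error on a 5% size is √(0.05 × 0.95/4,000) = 0.0034 in the first row and √(0.05 × 0.95/10,000) = 0.0022 in the others. The loss is 0.1 points for modest site differences, 0.7 for moderate and 3.7 for extreme.

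**4. Role of within-site balance.** The extreme setting was repeated with simple randomization inside each site (8,000 runs). The size of the plain test was then 0.051, so the conservatism disappears without enforced balance. The power gap remained: 78.4% against 82.9% for CMH.

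**5. Baseline NT-proBNP, no site effect.** Plain chi-square against a logistic score test with site and baseline:

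| Log-odds ratio per SD (assumed) | Size, chi-square | Size, adjusted | Power, chi-square | Power, adjusted |
|---|---|---|---|---|
| 0.5 (10,000 runs) | 0.050 | 0.051 | 78.8% | 81.1% |
| 1.0 (4,000 runs) | 0.046 | 0.048 | 79.1% | 84.9% |

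The 0.046 lies within simulation noise of 0.05 (standard error 0.0034). The gain is 2.3 to 5.8 points, and it does not come from an inflated size of the adjusted test.

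**6. Both effects strong** (site rates 16/30/50%, log-odds ratio 1.0; 4,000 runs). The plain test has size 0.039 and power 80.6%; the adjusted test has power 89.1%. This is an upper end, not an expectation.

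**The case against.** The strongest reply is that the protocol article is condensed, that strata and covariates are routinely set in an analysis plan not shown here, and that a general rule for categorical variables does not exclude a stratified primary analysis there. This lowers the weight of the point. It does not remove it, because the article is not silent: it names a test, and that test does not use the stratification it describes.

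Second, the documents give reasons to expect small site differences. NT-proBNP is measured in one laboratory, eligibility is uniform, and background care follows one national guideline. This stands as a reason to give most weight to the modest and moderate rows. That one centre is by name a TCM hospital says nothing about response rates.

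A reader might also infer four stronger things, none of which the documents support:

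- *That the plain test is certainly conservative.* This needs both site differences in response and balance within site. The protocol reports neither site rates nor blocks. Stratifying has little purpose without enforced balance, so blocking is likely, but it is an assumption.
- *That ignoring baseline NT-proBNP also makes the test conservative.* Baseline is not a stratification factor, and size stays at about 0.05 without it. The endpoint is also already relative to each patient's own baseline, so how far baseline predicts response is unknown.
- *That this choice takes the trial below its planned 80% power.* The sample size formula assumes an unadjusted comparison, so adjustment would be a gain over plan. With 200 × 0.8 = 160 evaluable patients, or 80 per arm, power is 77.2% (pooled) or 78.6% (unpooled). That shortfall comes from the dropout inflation and is a separate issue.
- *That the result would be invalid.* Any error is on the safe side.

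**Conclusion.** The mismatch between design and named test is real, and its consequence is small. On assumed modest to moderate site differences with balanced allocation, the cost is a slightly conservative test and less than 1 point of power. It reaches about 4 points only if placebo response runs from 13% to 53% across sites. Most of the available gain would come from baseline NT-proBNP, and only if it is prognostic at about the strengths assumed. All the sizes rest on assumed effects, roughly equal sites and 83 evaluable patients per arm. Type I error is not inflated under any of these settings. The point is a worthwhile improvement in efficiency and consistency, not a validity error.

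**What to change.** Amend the Data analysis section before unblinding so that it names the primary test separately from the general rule for categorical variables. The minimum is a Cochran-Mantel-Haenszel test stratified by study site. The preferred form is logistic regression on arm, site and log baseline NT-proBNP, with the result reported as a standardized (marginal) risk difference and its 95% CI. That keeps the estimate on the scale of the two proportions used for the sample size. Keep the plain chi-square test as a supportive analysis. If an analysis plan already specifies a stratified or adjusted primary test, bring the protocol text into line with it.

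The cost is one sentence. Site is known for every patient and baseline NT-proBNP is already collected before dosing, so no new data are needed, and this change does not require a different sample size.

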## Blinding

Participants, investigators, and the clinical trial pharmacist will be blinded to the treatment allocation throughout the course of the study. The placebo granules will be similar to the QSG granules in appearance, taste, and smell. The manufacturer will label the random codes on the packaging, and the code labeling will conform to the principles of GCP. The clinical trial pharmacist at each center will provide the packaged drugs to the participants according to the randomization number. The statistician will uncover the blinding when necessary, in case a serious adverse event (SAE) occurs, which includes death, life-threatening, hospitalization, prolonged hospitalization, or causing a permanent disability, cancer, birth defects, and drug overdose.

## Intervention

### QSG

The QSG treatment group will receive *Qishen* granules (13.6 g/pouch, twice per day—30 min after breakfast and dinner—for 12 weeks; dosage based on the requirements of Pharmacopoeia of the People’s Republic of China). The *Qishen* granules are manufactured by Beijing Tcmages Pharmaceutical Co., Ltd. (Beijing, China), a company that has obtained Chinese Good Manufacturing Practice for Pharmaceutical Products certification. All the ingredients have been approved by the Chinese Ministry of Food and Drug Safety. The 13.6 g (net weight) of granules (dehydrated ingredients combined with dextrin and caramel) are composed of six herbs: *Astragalus membranaceus* (Fisch.) Bge. var. *mongolicus* (Bge.) Hsiao (6 g), *Salvia miltiorrhiza* Bge. (1.5 g), *Lonicera japonica* Thunb. (2 g), *Scrophularia ningpoensis* Hemsl. (2 g), *Aconitum carmichaeli* Debx. (0.9 g), and *Glycyrrhiza uralensis* Fisch. (1.2 g).

### Placebo

The placebo group will receive placebo granules (13.6 g/pouch, twice per day—30 min after breakfast and dinner—for 12 weeks). The placebo is also manufactured by Beijing Tcmages Pharmaceutical Co., Ltd. (Beijing, China) by conforming to the specification for processing Chinese medicine in Beijing. The placebo granules are similar to the *Qishen* granules in appearance, taste, and smell.

All products will be packaged by Beijing Tcmages Pharmaceutical Co., Ltd. (Beijing, China). Either QSG or placebo pouches will be provided to each randomized participant at visit 1 (week 0 ± 3 days), visit 2 (week 4 ± 3 days), and visit 3 (week 8 ± 3 days).

